### Outcome Measures

#### Primary Outcome Measure

We will evaluate the short-term effects of Retrieval-TBS treatment in the reduction of cue-induced drug craving and cue reactivity by comparing EEG in VR scene between baseline (T0) and post-test (T3).

***EEG*** will be recorded by a portable EEG system (Muse by Interaxon Inc.) during each VR session (3 min/scene × 1 MA-related VR scene and 1 neutral-related VR scene = 6 min) at T0 and T3, respectively. Each patient will wear an EEG headset before entering the VR scenes. Four channels (refer to EEG 10-20 system: FP1, FP2, TP9, TP10) and an original reference (FPz) will be retained to measure the brainwave spectrum including delta, theta, alpha, beta and gamma (with a sample rate of 256 Hz and 12 bit resolution), frequency bands between 45 and 60 Hz were omitted because muse hardware applied notch filters at 50 and 60 Hz to reduce environmental noise (67). According to a previous study, there was a significant difference between drug-cue and neutral-cue-induced EEG activities (68). In terms of drug-cue related memory, the frontal theta activity used as a feedback signal in adaptive regulation was highlighted for memory updating (69), which has been suggested as an indicator of the enhanced binding of incoming interconnected information in memory formation (70), while the beta activity which reflects a memory promoting state (70) indicated the level of memory integration in reconsolidation (71). Since the wearable devices available in VR have been applied to classify emotional states (72), we plan to use wearable EEG combined with VR scenes to observe the brain activity associated with memory in the current study. The average power in EEG frequency bands (i.e., δ = 1–4 Hz, θ = 4–8 Hz, α = 8–13 Hz, β = 13–30 Hz, γ = 30–50 Hz) are real-time computed in hardware and sent alongside an indicator of data quality from each sensor. The Muse manufacturer provided on-device computed FFTs (https://sites.google.com/a/interaxon.ca/muse-developer-site/museio) were used to estimate the spectral power density (μV2/Hz) for frontal electrodes in each frequency band in this study. EEG spontaneous measures at the frontal sites were calculated, as shown in Figure 2, by 1 min post-dark data minus 1 min pre-dark data in each frequency band in each VR scene. We used state-related EEG to calculate the EEG activities for drug-related craving state in VR, because cue-induced craving is related to a tonic, slowly changing craving state and Muse is a portable device that may not stably acquire EEG activities during walking in VR scene. Previous studies have used “state-related EEG” to compare different EEG activities in different state (56, 72, 73). Because of the non-normal distribution, power density value and ratios were log-normalized. For statistical tests, a two-tailed alpha of 0.05 was used unless explicitly stated otherwise.

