#### Data Preparation and Descriptive Statistics

After inspecting original data, identifying unusual cases, transforming and summarizing data-sets according to different types of variables: the mean, median, standard deviation, ranges and valid samples will be required at first, as well as the counts and percentages specific for categorical variables. Firstly, running SPSS 21.0 for basic check of validated data both based on the extent of treatment completion (>85%) and accepted level of missing/obscure/contaminated data (<10–20%). The missing data will be estimated via multiple imputations. Secondly, the distribution of data will be analyzed both by stem-and-leaf plot (SPSS 21.0), the actual data calculated for normality overlay a normal curve will be required to determine that to what extent it is a normal distribution (without significance at given alpha = 0.05). For a poor fitted normal curve, non-parametric inferential will be selected, while the standard or similar standard alloy will run the parametric inferential.

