#### Inferential Statistics to Determine the Efficiency of Intervention

The statistical significance (sig) and effect size (ES) will be evaluated for treatment-effects determination either by paired *t*-test and repeated measures ANOVA test [two factors, test time (baseline vs. post-test) and treatment (MA VR scene + TBS vs. MA VR scene + sham TBS vs. neutral VR scene + TBS)] in parametric estimations or Friedman's chi-square and Kendall's W coefficients in non-parametric statistics. These differences between baseline and post-tests will be compared firstly between the three parallel groups for self-reported craving and neurophysiological measures (e.g., EEG and ECG).

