#### Regression Analysis for Variables Prediction

A generalized linear modal (GLM) will be used for regression analysis of co-variation (e.g., emotion and mood state) and of the follow-up long-term effects by SPSS 21.0. The selected model with different statistics will be specified based on data characteristics such as the type of distribution. For example, a multiple linear regression model will be introduced according to stepwise regression to test whether there was any potential influencing factor among secondary indicators.

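### A normality check on the observed values, not on changes or residuals, decides whether the between-arm ANOVA is run or replaced by a test that does not compare arms

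*Protocol article*

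**What the plan says.** The section on data preparation and descriptive statistics first provides for inspection and transformation: "After inspecting original data, identifying unusual cases, transforming and summarizing data-sets according to different types of variables". It then describes the normality check: "the actual data calculated for normality overlay a normal curve will be required to determine that to what extent it is a normal distribution", with the criterion "without significance at given alpha = 0.05". The consequence is stated as a rule: "For a poor fitted normal curve, non-parametric inferential will be selected"; otherwise parametric methods are used. Neither model residuals nor baseline-to-post changes are named as the quantity to be checked.

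The section on inferential statistics gives the two branches. The parametric one is a paired t-test and a "repeated measures ANOVA test [two factors, test time (baseline vs. post-test") by three-arm treatment factor. The non-parametric one is Friedman's chi-square and Kendall's W. The same section says that the aim is to compare the baseline-to-post differences between the three parallel groups.

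For the primary outcome, the EEG measure is itself a difference, formed "by 1 min post-dark data minus 1 min pre-dark data in each frequency band in each VR scene", and it is logged: "Because of the non-normal distribution, power density value and ratios were log-normalized". VAS craving and heart rate are secondary outcomes, and no such differencing or log is stated for them.

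**The concern.** Two things are wrong with the trigger. First, it looks at the wrong quantity. With two occasions, the time-by-treatment test depends on the data only through each person's T0-to-T3 change. A skewed or clustered spread of levels between people cancels out of that test, yet it can fail the normality check and send the outcome to the other branch. Second, a check at 0.05 fails some perfectly normal data by chance, so the analysis of each outcome is settled only after its data are seen.

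At stake is which question gets answered. The branch that the rule leads to has no arm factor, so a needless switch replaces the arm comparison with a test of change over time. Bands, craving and heart rate could also end up under different kinds of test within one report.

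**Working it through.** **Plan's own figure.** The protocol gives no error rate for the switching rule. The related figure is the sample size of 45, computed for the within-by-between ANOVA interaction. With the stated f = 0.2496, 3 groups and 4 tests, and assuming correlation 0.5 and no sphericity correction, λ = f²·N·m/(1−ρ) = 0.0623 × 45 × 4 / 0.5 = 22.4 on 6 and 126 df. Power is then 0.955 and the required N is 45. So the trial was sized for the test that the rule may discard.

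**What the ANOVA needs.** In a 3 × 2 repeated-measures ANOVA, the interaction F equals the one-way F on change scores. On one simulated data set with skewed person levels both were 0.72373. Only the within-arm changes need to be near normal.

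**Chance switching.** For one outcome checked at T0 and T3, treating the two checks as independent: 1 − 0.95² = 0.098.

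**Simulation.** There were 15 people per arm, within-person error variance 0.5 at each occasion (so the SD of change is √(0.5 + 0.5) = 1), Shapiro-Wilk at 0.05 on all 45 values at each occasion, and 3,000 or more trials per scenario. The level distributions and the choice of Shapiro-Wilk are assumptions.

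| Scenario (changes normal throughout) | Rule leaves the ANOVA | True error of the ANOVA |
|---|---|---|
| Normal person levels | about 10% | about 5% |
| Lognormal person levels (sigma 0.8), undifferenced outcome | about 85% | 5.1% |
| Same lognormal levels, score formed as post-dark minus pre-dark | 9.8% | about 5% |

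In the second row the change residuals fail the same check in only about 5% of trials, so a check on the right quantity would not have switched. Other non-normal level shapes (uniform, exponential, two clusters) gave switching in 34 to 99% of trials. Normal levels, however wide, gave only the chance rate.

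**Cost with a sound fallback.** With a shift of 1.25 in one arm and lognormal levels, the ANOVA always run has power 0.938. Switching to a Kruskal-Wallis test on changes gives 0.923, a loss of 1.5 points.

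**Cost with the named fallback.** With two occasions, pooled over arms, Friedman's statistic is (2k − 45)²/45, where k is the number of people whose value rises. Arm membership does not enter. Suppose that every arm falls by 0.8 and the arms do not differ. Each person then rises with probability Φ(−0.8) = 0.212, so k is about 9.5 and the statistic is about (19.1 − 45)²/45 = 14.9, against a critical value of 3.84. In simulation Friedman rejected in 97.8% of such trials and the ANOVA in 5.1%. For the two-stage rule, approximately:

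- normal data: 0.098 × 0.978 + 0.902 × 0.05 = 0.141;
- lognormal levels: 0.84 × 0.978 + 0.16 × 0.05 = 0.830.

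Direct simulation of the two-stage rule gave 13 to 14% and 83%.

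**The case against.** The strongest reply is that the primary outcome is largely protected from the level problem. The EEG score is a within-scene difference on logged power, so a stable additive person level has gone before any check is made, and switching falls to the chance rate. This stands. A reader might infer that the primary EEG test is usually lost because people differ in level; the documents do not support that. Nor is the check necessarily on untransformed values, since transformation comes first.

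It can also be said that the protocol names no specific test. It mentions a stem-and-leaf plot and a curve overlay, and it seems to tolerate approximate normality. That is fair, so the percentages depend on a strict reading. The 0.05 criterion is nevertheless written down, and a judgement by eye would leave the choice of test less fixed, not more.

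Third, switching by itself costs little. In the skewed scenario the ANOVA is both run and significant in only about 19% of trials, where it would detect the effect in 94%. A reader might take this as a power loss. It is not one, because it counts every switched trial as a failure whatever the second test finds; with a valid rank test the loss is 1 to 2 points. What survives is that the second test named here is not such a test.

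Finally, the regression section's sentence "The selected model with different statistics will be specified based on data characteristics such as the type of distribution" may look like the same rule. It concerns covariates and long-term effects, and states no normality test, no threshold and no non-parametric branch. It is not part of this point.

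**Conclusion.** The point holds in a limited form. The rule checks the wrong quantity and leaves the test for each outcome unfixed until the data are seen. The chance of discarding a valid arm comparison is about 10% per outcome under a strict Shapiro-Wilk reading with one check per occasion. For undifferenced outcomes it could be far higher, about 85% under the assumed lognormal levels, but whether VAS or heart rate levels are skewed in that way is not known from the documents. For the EEG score only the 10% is shown, reading the score as a difference of log power. Ten independent checks (five bands, two occasions) would give 1 − 0.95¹⁰ = 40.1% for at least one switch. The bands come from the same people and recordings, so that figure is illustrative only.

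The practical importance comes from pairing this trigger with a fallback that does not compare arms. With a common fall and no arm difference, the two-stage procedure can report significance in about 13 to 14% of trials (normal data) to 83% (skewed levels), against 5% for the ANOVA. This assumes Friedman's test pooled over arms, since the protocol does not say how it would be run; run within each arm, it would still not compare the arms. The rule should be changed.

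**What to change.** 1. In the data preparation section, delete the sentence that lets the normality result choose the family of tests.
2. In the inferential statistics section, name one between-arm analysis for each outcome: the linear model for T0-to-T3 change, or for T3 adjusted for baseline, with EEG power on the log scale. State that it is run whatever a normality check shows.
3. Inspect the residuals of that model instead of the distribution of observed values, and report what is seen.
4. Report a rank or permutation test of the between-arm difference in T0-to-T3 change as a fixed sensitivity analysis, in place of Friedman's chi-square and Kendall's W for this comparison.

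The cost is a few sentences in two sections and one extra results table. Recruitment, visits and measurements do not change.

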#### Inferential Statistics to Determine the Efficiency of Intervention

The statistical significance (sig) and effect size (ES) will be evaluated for treatment-effects determination either by paired *t*-test and repeated measures ANOVA test [two factors, test time (baseline vs. post-test) and treatment (MA VR scene + TBS vs. MA VR scene + sham TBS vs. neutral VR scene + TBS)] in parametric estimations or Friedman's chi-square and Kendall's W coefficients in non-parametric statistics. These differences between baseline and post-tests will be compared firstly between the three parallel groups for self-reported craving and neurophysiological measures (e.g., EEG and ECG).

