### Sample Size

According to Hanlon et al. (28) study, 25 cocaine users either receiving active- or sham- pre/post TBS treatment showed a significant difference in the reduction of cue craving (*F*_1, 96_ = 5.65, *P* = 0.02). The effect size (*f*= 0.2496) calculated by formula $r^{2}=\frac{df1^{*}F}{df1^{*}F\;+\;df2},f=\sqrt{\frac{r^{2}}{{1-r}^{2}}}$, the 3 (between factor: MA VR-active TBS vs. MA VR-sham TBS vs. neutral VR-active TBS) × 4 (within factor: four repetitive tests) design of the current protocol, the proposed alpha error (α = 0.05) and power (β = 0.95) will be used as the parameters for a prior sample size calculation (in G.Power 3.1). The required sample size is 45 in terms of repeated measures ANOVA with within × between interaction effect.

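### With only baseline and post-test, the planned repeated-measures ANOVA is a 2-df test on change scores: valid, but less precise than baseline adjustment and unable on its own to show that A beats both B and C

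*Protocol article*

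**What the plan says.** The section on inferential statistics names a paired t-test and a "repeated measures ANOVA test [two factors, test time (baseline vs. post-test) and treatment" with the three arms as levels, or Friedman and Kendall statistics if the data are not normal. It continues: "These differences between baseline and post-tests will be compared firstly between the three parallel groups". The section on the primary outcome measure sets the comparison as T0 against T3. It defines the EEG measure as the minute of darkness after a scene minus the minute before it, at the frontal sites, log-normalised, and states that "a two-tailed alpha of 0.05 was used unless explicitly stated otherwise".

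The Sample Size section says: "The required sample size is 45 in terms of repeated measures ANOVA with within × between interaction effect".

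No section adjusts for the outcome's own baseline value, and none names an A-B or A-C contrast. The generalised linear model under the regression heading is for emotion and mood covariates and for follow-up effects.

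**The concern.** The arms in Study Design were chosen to answer two questions. A against B isolates active stimulation after drug-cue retrieval. A against C isolates drug-cue retrieval before active stimulation. A reconsolidation effect needs both differences. A three-group F asks only whether the arms differ somewhere, and B against C alone can make it significant. The paired t-test is within-group and makes no comparison between arms.

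A change score also fixes the baseline coefficient at 1 instead of estimating it. With 15 per arm this uses the baseline inefficiently and lets chance imbalance at T0 add noise. The stakes are avoidable loss of precision in a 45-person trial, and a primary test whose significance would not identify the effect being claimed.

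**Working it through.** **Inputs from the protocol.** Three arms of 15, T0 and T3, two-sided alpha 0.05, target power 0.95, f = 0.2496, four repeated tests in the sample-size model.

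**Assumed.** Correlation rho between T0 and T3 (range 0.3 to 0.8), equal SDs at both visits, sphericity. Differences are in units of the single-visit SD.

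**1. The plan's own figure.** For the within-between interaction, lambda = f² × N × m / (1 − rho), with df (k−1)(m−1) and (N−k)(m−1). With m = 4 ("within factor: four repetitive tests") and rho = 0.5, lambda = 0.0623 × 45 × 4 / 0.5 = 22.4 on 6 and 126 df. Power is 0.955, so N = 45 reproduces. The planned primary analysis has m = 2: lambda = 0.0623 × 45 × 2 / 0.5 = 11.2 on 2 and 42 df, and power is 0.83.

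**2. Equivalence.** On one test data set, the mixed-ANOVA interaction F and the one-way F on change scores were both 0.61599.

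**3. Precision.** In units of SD², the change-score variance is 2(1 − rho) and the ANCOVA variance is 1 − rho². Their ratio is (1 + rho)/2, multiplied by 1 + 1/40 for estimating the slope.

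| rho | change | ANCOVA | ratio | with slope term | reduction |
|---|---|---|---|---|---|
| 0.3 | 1.40 | 0.91 | 0.65 | 0.67 | 33% |
| 0.5 | 1.00 | 0.75 | 0.75 | 0.77 | 23% |
| 0.7 | 0.60 | 0.51 | 0.85 | 0.87 | 13% |
| 0.8 | 0.40 | 0.36 | 0.90 | 0.92 | 8% |

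The gain vanishes at rho of about 0.95, where 1.025 × (1 + rho)/2 = 1.

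**4. Power, with A better than B = C by an assumed 0.9 SD.** For A-B at rho = 0.5, the change-score SE is √(2 × 1.00/15) = 0.365. The ANCOVA SE is √(2 × 0.769/15) = 0.320. The noncentralities are 2.46 (42 df) and 2.81 (41 df). For the omnibus F, lambda = 10 × 0.81 / [2(1 − rho)].

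| rho | A-B, change → ANCOVA | both contrasts, ANCOVA | planned omnibus F |
|---|---|---|---|
| 0.3 | 53% → 70% | 56% | 52–54% |
| 0.5 | 68% → 78% | 68% | 69% |
| 0.7 | 88% → 92% | 86% | 89–90% |
| 0.8 | 97% → 98% | 95% | 98% |

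Like for like at rho = 0.5, power for both contrasts rises from about 55% to 68%. A second simulation gave 53% to 67%, so read these to within about two points.

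**5. What the omnibus F can pick up.** The plan's f at two time points corresponds to one arm differing by √(11.2/10) = 1.06 SD. If that arm is C and A = B, then at rho = 0.5 the planned F is significant in 83% of simulated trials. Both contrasts are significant in 3% on change scores and 4% with ANCOVA.

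**The case against.** The planned ANOVA is a valid analysis of a randomised trial, and replacing a valid test with a more efficient one can look like preference. A condensed article may leave contrasts to an analysis plan that is not shown, and the word firstly in the comparison sentence leaves room for follow-up tests.

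Much of this stands, and it rules out several stronger readings:

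- **That the planned test is biased or inflates type I error.** It does neither. The point is efficiency and targeting.
- **That the protocol will claim reconsolidation from the omnibus F alone.** No section says so. What can be said is that the named test cannot isolate the effect and that no contrast is named to do it.
- **That the change raises power for the trial's claim by ten points.** The rise from 68% to 78% is for A-B alone. Requiring both contrasts gives 68%, against 69% for the planned F, and falls below the planned F at higher correlations.
- **That adjustment at rho = 0.5 saves 25%, or is worth 60 participants instead of 45.** That ignores estimation of the slope. The figure is 23%, or 45/0.769 = about 58.5 participants.

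The objection does not remove the point. The model and its two time points are stated, not left open, and the section that adds covariates does not mention the outcome's baseline.

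**Conclusion.** The concern holds as one of precision and targeting, and the change should be made. The equivalence to a change-score ANOVA, and the inability of a 2-df test to show A better than both B and C, need no assumed values. The sizes do: rho, equal SDs and the 0.9 SD advantage are assumptions. Within rho 0.3 to 0.8, the variance reduction runs from about 33% to 8%. Baseline adjustment helps any given contrast throughout that range. The both-contrasts rule adds specificity, at equal power to the planned F at rho = 0.5 and a cost of about 3 points at 0.7 and 0.8.

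**What to change.** In the inferential statistics section, make the primary parametric model the T3 value of the EEG measure as the protocol defines it (post-dark minus pre-dark minute, frontal, log-normalised as stated) on arm plus the same measure at T0. Use the same model for VAS craving and heart rate. Report planned A-B and A-C contrasts with 95% confidence intervals. Claim a reconsolidation effect only if both favour A and are significant at two-sided 0.05. Because both must succeed, this joint claim needs no alpha split. Keep the omnibus F as supportive.

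The cost is one error degree of freedom (42 to 41) and revised wording, with no new data or visits. The Sample Size section must also change, because N = 45 was derived for a four-measurement interaction F. Power at N = 45 should be restated for the two contrasts over a stated range of rho. The non-parametric branch is not covered by this change.

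Suggested wording: *The T3 value will be analysed by ANCOVA with arm as factor and the T0 value of the same measure as covariate. The A-B and A-C differences will be given with 95% confidence intervals; a reconsolidation effect will be concluded only if both favour A at two-sided 0.05.*

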## Methods/Designs

### Study Design

This is a randomized, sham-controlled double-blind study. Participants will be randomly assigned by main investigator to three parallel groups using computer-generated random numbers with a 1:1:1 allocation ratio, either receive (1) MA-related cues retrieval in VR combined with active TMS (group A: MA VR scene + TBS) or (2) sham TMS (group B: MA VR scene + sham TBS), or (3) neutral cues retrieval in VR combined with active TMS (group C: neutral VR scene + TBS). Participants, outcome assessors, and data analysts will be blinded to the group assignment during treatment sessions. The doctors delivering TMS treatment will know the allocation sequence but will not be involved in the assessment. Once treatment is completed, participants will be asked to guess the specified intervention they have received to determine the actual effect of TBS. Then the clinical evaluator will debrief the participants about the study procedures. The two “VR retrieval–TBS” treatment sessions will be scheduled in 2 days within 1 week using an MA-related or neutral VR scene. Clinical, psychological questionnaires and EEG will be carried out at baseline (T0), each treatment session (T1/T2), the week of the last treatment (T3) and over 1 month after treatment (T4), as shown in Figures 1, 2. This protocol follows SPIRIT recommendations.

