
#### Secondary Outcome Measures

The secondary outcome will focus on the long-term effects of repetitive treatments on drug-cue-induced response. Evaluations introduced in primary outcome will also be collected in the follow-up test (T4). Furthermore, self-reported craving in VAS as a subjective indicator for cue-induced drug craving, physiological parameter (cue-induced heart rate) and possible co-variables corresponding to substance-taking history, emotional and mental state will be measured with the clinical diagnosis and psychological questionnaires at baseline (T0), post-test (T3) and follow-up test (T4) respectively.

***VAS*** embedded in VR scenes is a 100-point visual analog scale ranging from 0 (no craving) to 100 (high craving) for self-reported craving. Each patient will be directed to evaluate their current craving at a black screen on one wall of a virtual room. They will be guided to focus on their momentary feeling to make an assessment. The VAS points at baseline (T0) will be compared with the post-test after the last treatment (T3) to identify an expected reduction in self-evaluated craving. The median, range, average and standard deviation of VAS will be calculated for analysis.

***Electrocardiography (ECG)*** Given the association of MA with autonomic nervous system dysfunction (74) and the significant difference in heart rate between drug-cue and neutral-cue in the cue-induced craving paradigm (75), ECG (BIOPAC ECG module, with sampling rate of 1,000 Hz) will be recorded in this experiment as an indicator of physiological changes. In addition, changes in the heart rate interval can reflect abnormalities of autonomic nervous function (76). In addition, its activities are related to executive functions such as working memory, attention maintenance, and response inhibition involved in prefrontal cortex activities (77). In MA studies, it shows significantly reduced heart rate variability in MA populations (76), and the difference between drug-cue and neutral-cue is significantly associated with subjective cravings (78). Therefore, ECG will be recorded at the same time with EEG.

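### When the normality check fails, the only tests named for the treatment effect (Friedman, Kendall's W) cannot compare the three arms

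*Protocol article*

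**What the plan says.** The Study Design section describes allocation to "three parallel groups using computer-generated random numbers with a 1:1:1 allocation ratio", so the arms are independent groups and not matched sets.

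In Data Preparation and Descriptive Statistics, the observed distribution decides the type of analysis: "For a poor fitted normal curve, non-parametric inferential will be selected".

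In Inferential Statistics to Determine the Efficiency of Intervention, significance and effect size "will be evaluated for treatment-effects determination either by paired *t*-test and repeated measures ANOVA test", the ANOVA having "two factors, test time (baseline vs. post-test) and treatment" as its terms. The alternative, for data that fail the check, is "Friedman's chi-square and Kendall's W coefficients in non-parametric statistics". The next sentence gives the aim: "These differences between baseline and post-tests will be compared firstly between the three parallel groups".

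The Sample Size section arrives at 45 participants from the within-by-between interaction of a repeated measures ANOVA.

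The Primary Outcome Measure section adds, for the EEG data: "Because of the non-normal distribution, power density value and ratios were log-normalized".

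**The concern.** The question that randomisation answers here is whether the change from T0 to T3 differs between arms. Friedman's test asks whether measurements differ between occasions within people, and Kendall's W is the same statistic rescaled as an effect size. A change shared by all arms makes these statistics large. A difference between arms affects them only through the average movement over arms.

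A shared change is plausible in this trial. All arms meet the same test scenes at T0 and T3. People who do not respond to the VR scene at baseline are not enrolled, which invites regression to the mean. If the fallback were applied as written, a general decline could be reported as a treatment effect, and a real difference between arms could be missed.

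**Working it through.** **1. The plan's own figure.** Inputs from the Sample Size section: f = 0.2496 (taken as printed), 3 groups, 4 measurements, alpha 0.05, power 0.95. Assumed, because not stated: correlation 0.5 and sphericity. For the interaction:

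- noncentrality = N × f² × m / (1 − rho) = 45 × 0.0623 × 4 / 0.5 = 22.4
- df1 = (3 − 1)(4 − 1) = 6; df2 = (45 − 3)(4 − 1) = 126
- power = 0.955 at N = 45, and 0.938 at N = 42

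So 45 reproduces, and the effect sized for is group by time.

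**2. What the fallback tests.** With two occasions and n participants, let n₊ rise and n₋ fall. Then:

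- Friedman chi-square = (n₊ − n₋)² / n, on 1 df
- Kendall's W = chi-square / [n(m − 1)] = chi-square / n when m = 2

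This is a sign test of change over time. Arm appears in neither formula. Friedman's test could compare arms only if participants were matched in blocks of three, and they are not.

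**3. No treatment effect, same fall in every arm.** Assumed: 15 per arm, bivariate normal data, correlation 0.5, common fall of 0.5 SD. The change then has SD √[2(1 − 0.5)] = 1, and each participant falls with probability q = Φ(0.5) = 0.69. The critical value is 3.84.

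- *Pooled over 45:* significant when at least 30 fall (15²/45 = 5.0; with 29, 13²/45 = 3.76 is not enough). P(Bin(45, 0.69) ≥ 30) = 0.70.
- *One arm of 15:* significant when at least 12 fall (9²/15 = 5.4; with 11, 7²/15 = 3.27 is not enough). P(Bin(15, 0.69) ≥ 12) = 0.27.
- *A significant, neither control:* 0.273 × (1 − 0.273)² = 0.14.
- *A significant, not both controls:* 0.273 × (1 − 0.273²) = 0.25 (24% to 25% by simulation).
- *Kruskal-Wallis on T3 − T0 change:* about 5% by simulation.

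| Common fall | Friedman pooled | A and neither control | A but not both controls | Kruskal-Wallis on change |
|---|---|---|---|---|
| 0.5 SD | 70% | 14% | 25% | about 5% |
| 0.8 SD (q = 0.79) | 98% | 9–10% | 38% | about 5% |

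**4. A real difference that averages out.** Assumed: subject SD 1, error SD 1, changes of −1, +0.5 and +0.5 in the three arms, 10,000 simulated trials. Pooled Friedman is significant in 2.5% (normal errors) or 3.7% (lognormal errors). Kruskal-Wallis on change is significant in 80% or 98%.

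**The case against.** **The arms are compared elsewhere.** A reader might infer that the paired t-test leaves the parametric branch with the same gap. It does not. The paired t-test alone cannot show a treatment effect, but it stands beside an ANOVA with time and treatment, whose interaction is the between-arm test of change. A reader might also infer that the plan has no aim of comparing groups. It states that aim directly, and careful analysts might act on it. Both objections stand, and they confine the fault to a mismatch between the stated aim and the tests named for non-normal data.

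**The generalized linear model could fill the gap.** The regression section lets the model follow the distribution, but assigns it to covariates and to the long-term follow-up. It is not offered as the T0 to T3 comparison of arms.

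**A separate analysis plan may settle it.** It may. But this is not detail left for later: the article names the fallback, and the one it names does not fit the design.

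**The fallback may never be used for the primary outcome.** The remark on non-normal EEG power explains a log transformation already applied. Whether log power would still fail the check cannot be known from the document. The 0–100 craving scale has no stated transformation and could plausibly fail, but it is a secondary outcome. This objection stands in full.

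**The error rates are constructed.** The common fall and the correlation are assumed, and the article does not say whether Friedman's test would be pooled or run by arm. Normal data are an odd assumption for a branch used when normality fails. That last point matters less than it seems, because the Friedman rates depend only on q, the chance that a participant falls. The looser by-arm criterion also counts trials in which one control is significant too. The stricter 14%, which drops to 9–10% at 0.8 SD, is the fairer figure for a clean false claim.

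**Conclusion.** The concern holds for the non-parametric branch only. The tests named there cannot compare three independent arms, so that branch provides neither the stated group comparison nor the interaction used for sizing. This follows from the form of the statistics and needs no assumption.

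The size of the consequence is illustrative. Under the assumptions in the working, a shared fall of 0.5 SD with no treatment effect makes pooled Friedman significant in about 70% of trials and gives a clean false claim by arm in about 14%, against about 5% for a test that compares arms.

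The document does not support saying that the treatment effect will go untested in this trial. The parametric analysis tests it, and use of the fallback for the primary outcome is possible but not shown.

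**What to change.** In the section on inferential statistics, replace Friedman's chi-square and Kendall's W with a method that compares arms. Either of these would do:

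- Kruskal-Wallis on the T3 − T0 change, with A–B and A–C contrasts; or
- a rank-based or permutation ANCOVA of T3 adjusted for T0, with the same contrasts.

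State that within-arm tests, including the paired t-test and any Friedman test kept for change over time, are descriptive and carry no claim about treatment.

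The repeated measures ANOVA can remain as the parametric analysis. Replacing it with another model, or removing the normality check, is a separate matter and is not needed to cure this fault.

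The cost is a change of wording. It needs no extra participants, visits or measurements.
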